## Abstract

**Background:**

Burn patients experience severe pain when undergoing rehabilitation after skin grafting, which negatively affects their recovery. Traditional analgesic methods (such as opioids) have the risk of addictiveness and side effects. Nitrous oxide, which has rapid analgesic and sedative effects, is commonly used for conscious analgesia. The purpose of this study was to determine whether diluted nitrous oxide reduces pain compared to Placebo(oxygen) during rehabilitation after burn surgery.

**Method:**

This single-center, randomized, double-blind, and controlled trial will enroll 80 patients. Patients ≥ 18 years of age who underwent rehabilitation 1 month after burn surgery with acute pain (VAS ≥ 4) were included. The main exclusion criteria included: pulmonary disease (pulmonary embolism, pneumothorax), intestinal obstruction, etc. Patients were randomly assigned in a 1: 1 ratio to intervention (A) and control (B) groups. Doctors, therapists, patients, and data collectors were unaware of the assignment outcomes. Rehabilitation will be performed by a therapist. The nurse performing the intervention handed the envelope with the patient code and the A or B assignment to the physician. Group A will receive diluted nitrous oxide inhalation plus conventional therapy (without analgesics) 30 minutes once daily for 4 weeks, and Group B will receive oxygen plus conventional therapy (without analgesics) under the same conditions. Assessments will be performed before the intervention (T0), 2 minutes (T1) and 5 minutes (T2) after the start of the intervention, and 5 minutes (T3) after the start of the intervention. The primary outcome was pain score. Secondary outcomes included vital signs, side effects, quality of life score, scar score, need for adjuvant analgesia, therapist and patient satisfaction, and willingness to receive the same gas again.

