### Randomization, allocation, concealment and blinding

Randomization will perform by statistical experts, using SPSS 27.0 software randomly assigned patients 1: 1 to the intervention group versus the control group. The experimental group will be given nitrous oxide inhalation and conventional treatment, while the control group will be given placebo (100% oxygen) inhalation and conventional treatment. Before the trial begins, the project manager will prepare a series of opaque envelopes, each containing a card with treatment assignment written on it (“nitrous oxide group” or “placebo group”). When the patient meet the inclusion criteria and completed the baseline assessment, the project manager will randomly select an envelope from it and determine the allocation of the patient based on the card inside the envelope. Grouping will be confidential to patients and other investigators. The process of extracting the envelope is free from external interference, and the envelope is immediately destroyed to ensure the concealment of the distribution. The devices for both groups of gases are identical in appearance and are both labeled A or B. Neither the investigators nor the subjects involved in the trial could distinguish gases by smell and appearance. A researcher who is not involved in the evaluation will connect the patient to the gas device during the treatment and ensure the proper inhalation of the gas. Assessments will be performed independently by another investigator according to pre-set criteria and time points. During this trial, if the patient has serious side effects and other emergencies, the preset emergency unblinding procedure should be followed, and corresponding treatment measures should be taken to ensure the safety of the patient. Statistical analysts are also unaware of patients’ grouping and treatment measures.

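### The letters A and B name the arms in the abstract and also label the gas devices, and the arm letter goes to a physician listed as blind; as described, the coding does not secure the double blind

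*Protocol article*

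**What the plan says.** Three statements in the abstract (Method) fix what the letters mean: "Patients were randomly assigned in a 1: 1 ratio to intervention (A) and control (B) groups"; "Group A will receive diluted nitrous oxide inhalation plus conventional therapy"; and "Group B will receive oxygen plus conventional therapy (without analgesics) under the same conditions".

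The same paragraph says who is blind, "Doctors, therapists, patients, and data collectors were unaware of the assignment outcomes", and then describes a hand-over: "The nurse performing the intervention handed the envelope with the patient code and the A or B assignment to the physician".

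The section on randomization, allocation, concealment and blinding uses the letters again, now on the equipment: "The devices for both groups of gases are identical in appearance and are both labeled A or B". It says the gases cannot be told apart by look or smell. One researcher, who takes no part in evaluation, connects the gas, and another investigator assesses. Analysts are said to be blind. In this section the project manager draws the envelope, its card spells out the treatment in words, and the envelope is destroyed at once. An emergency route out of the blind is foreseen: "if the patient has serious side effects and other emergencies, the preset emergency unblinding procedure should be followed". Its details are not given in the article.

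**The concern.** A label that masks treatment must not itself identify the arm, and breaking it for one patient should say nothing about the next. The article describes two letters, gives their meaning in public, and places the same letters on devices used in front of patients and therapists. It also sends the letter to a physician, who belongs to a group listed as blind.

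The outcomes make this matter. The primary outcome is a self-reported VAS score taken during the session, and the Limitation section accepts that it is open to subjective influence. Satisfaction of patient and technician, willingness to use the gas again, use of adjunctive analgesics and the scar scale can also shift with expectation. If allocation were known, the likely direction of bias is towards nitrous oxide.

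**Working it through.** No effect estimate is involved, so the check sets the statements side by side and then counts how many patients share a code. The plan's power figure (91.67% with 9 per group at effect size 1.68) does reproduce: the exact two-sided t-test with 16 degrees of freedom and noncentrality 1.68 × √(9/2) = 3.56 gives 0.9167. It has no bearing on blinding.

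**Step 1: is the key public?** Yes. The abstract equates A with nitrous oxide and B with oxygen.

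**Step 2: do the same letters appear where blinded people could see them?**
- On the devices, according to the blinding section.
- In the envelope passed to the physician, according to the abstract.

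The article nowhere describes device letters being scrambled relative to the arm letters.

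**Step 3: do the two accounts of the envelope agree?**

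| | Abstract, Method | Blinding section |
|---|---|---|
| Content | patient code and A or B | treatment named in words |
| Handled by | nurse giving the intervention | project manager |
| What happens to it | passed to the physician | destroyed immediately |

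They differ on all three points. There may be two different envelopes, but the article does not say so.

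**Step 4: how far does one disclosure reach?** Inputs: 80 patients, 40 per group (Sample size estimation), and two letters, so 80 / 2 = 40 patients per letter. Suppose each letter is fixed to one gas, and let m be the number of patients whose letter a person can see. Learning what one letter means also settles the other, so the number decoded is m.

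| Situation | Allocations decoded |
|---|---|
| Knows the key, sees no patient's letter (m = 0) | 0 of 80 |
| Sees the letters of one group's patients (m = 40) | 40 of 80 |
| Sees every letter (m = 80) | 40 + 40 = 80 of 80 |
| Unique code per patient, one code broken | 1 of 80 |

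Step 4 does not need the published key. One emergency unblinding would be enough. So would a pattern of recognisable side effects on one letter: the Safety section lists drowsiness and euphoria among them and has therapists monitor for them, and the sessions are daily for 4 weeks.

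**The case against.** The strongest reply is that two links in the argument are not written down. The abstract uses A and B as names of arms and the blinding section uses them as device labels, but no sentence says that device A holds the gas of group A. Nor does the article say that the devices carry no other code; the abstract mentions a patient code, and how it relates to the devices is not described. Both points stand, so the conclusion rests on the natural reading. The shared-code weakness in Step 4 survives if the letters were merely swapped, but not if they were scrambled across patients or devices.

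Other protections are described and deserve credit: devices that look alike, gases that cannot be told apart, and separate people for connecting the gas and for assessment. They mask the gas and separate roles. They do not mask the letter from the patient, the therapist, or the physician who is handed it.

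A reader might infer more than the documents support:
- *The blind is already broken for all 80 patients.* No actual unblinding is shown. The figure of 80 is an upper limit that requires sight of every letter.
- *The published abstract alone reveals allocations.* It gives the key but no patient's letter, so by itself it reveals none.
- *The assessor reads the label.* Nothing says so, and the person who connects the gas is not the assessor.
- *The analyst works with the same letters.* The article does not say what the analyst receives; it says only that analysts are blind.

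The article condenses a fuller protocol, so the absence of detail on emergency unblinding is not a fault. The fuller text could restrict who learns the key. It could not restrict what that person then knows if the letters are fixed to the arms.

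Finally, side effects can let patients guess their own treatment under any labelling. Unique codes stop that guess from spreading to other patients; they do not protect the guessing patient's own VAS score.

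**Conclusion.** The concern holds as a defect in the coding as documented. Two things are explicit: the abstract sends the arm letter to a physician while listing doctors as blind, and the two accounts of the envelope disagree. A third follows on the natural reading: the device letters are the arm letters, so a person who knows the key and sees a letter knows that patient's treatment. One disclosure then decodes as many patients as have visible letters, up to 80 of 80, against 1 of 80 with unique codes.

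This assumes that device A corresponds to group A, or at least that each letter is fixed to one gas, and that no other code replaces the letters on the devices. The size of any resulting bias in the VAS cannot be estimated from the article. The sample size is unaffected.

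**What to change.** 1. Reconcile the abstract with the blinding section: state what the envelope contains, who opens it, who sees it and what becomes of it.
2. Do not give the arm letter to the physician or to anyone else listed as blind.
3. For patients not yet enrolled, replace the A/B device labels with unique patient- or device-specific codes. The list should be held by someone outside treatment, assessment and analysis, and unblinding should be by single code.
4. For patients already treated, report the coding actually used and who could see it. If the device letters matched the arms, qualify the double-blind claim in the trial report.

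The cost is a code list, relabelling, a short amendment, and a look-up by the person who connects the gas. No extra patients or visits are needed. Timing limits the gain: recruitment began on April 7, 2025 and was expected to take eight months, so item 3 helps only if enrolment is still open. Items 1 and 4 apply in any case. None of this prevents patients from guessing their own treatment from side effects.

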**Discussion:**

If the experimental results show that diluted nitrous oxide can bring good analgesic effects without serious side effects, it can improve patients’ compliance with rehabilitation treatment and quality of life, and it is even widely implemented in hospitals and rehabilitation institutions.

## Introduction

Burn hypertrophic scars(HSs) are a matter of great concern to patients and doctors. Poor wound healing can lead to scar contracture, which is the most harmful complication after common burn surgery [1]. In the process of deep burn wound healing, due to the long-term existence of fibroblasts, the formed scar tissue is easily in a state of poor flexibility and high tension, which will not only aggravate the mechanical stimulation of the burn site, lead to pain and itching, but also cause long-term scar contracture. It will also lead to the loss of motor function of patients and cause bone and joint deformity, thus affecting the quality of life of patients [2–4]. Pressure suits control collagen synthesis by restricting blood supply, oxygen, and nutrient access, thereby inhibiting HSs growth. Although pressure suit therapy has been shown to help reduce HSs, rehabilitation exercises such as exercise, splint, massage, etc. guided by a rehabilitator can effectively prevent or reduce scar contracture and promote functional recovery [5]. Patients with burns may experience decreased mobility caused by fixation sequelae, ventilator dependence, and burn-related catabolic reactions [6]. Hypermetabolism after burns can lead to loss of muscle mass, resulting in rapid onset muscle fatigue [7]. Therefore, the focus of rehabilitation exercise for burn patients is to minimize scar hyperplasia and contracture; Improves flexibility, strength and endurance; And to promote independence in daily activities, including self-care and social and recreational activities.

Operative pain triggered by wound debridement, physical therapy, and rehabilitation exercises exacerbate the suffering of burn patients [8]. Poor pain control can lead to severe sequelae, including post-traumatic stress disorder (PTSD), acute stress disorder (ASD), depression, decreased mobility, delayed return to functional status, opioid dependence, and chronic pain syndrome, among others [9]. Good pain control and wound healing are considered very important throughout the burn recovery process. Despite the significant effect of opioids on acute pain, they carry a high risk of developing adverse effects such as delayed wound healing, respiratory depression, opioid-induced hyperalgesia, pruritus, acute urinary retention, opioid tolerance, dependence, addiction, and overdose-related death [10]. In recent years, music, hypnosis and virtual reality have been found to be useful non-drug analgesic measures. But because these are just relaxation and distraction techniques, it is difficult to achieve the same level of analgesia as medications.Many studies have shown that nitrous oxide can provide significant analgesic effects in different procedures, for example, dental surgery sedation and analgesia [11], acute injury sedation and analgesia [12], cancer pain [13], bone marrow biopsy [14], invasive operation in pediatrics [15],and labor analgesia,etc [16]. Patients inhale the gas through the self-controlled valve, and the common side effects are dizziness, nausea, vomiting, etc., which can disappear within five minutes after stopping the drug. Under the premise of strict control of contraindications, no serious complications have been found.

There is currently a lack of trials evaluating the efficacy of nitrous oxide in the treatment of pain during rehabilitation training in burn patients. Therefore, the aim of this study was to evaluate the analgesic effect of N2O in burn patients undergoing rehabilitation training by means of a randomized double-blind controlled trial. We hypothesized that its analgesic properties would reduce pain during rehabilitation training in burn patients with few side effects compared to placebo.We designed this study protocol to test and verify this hypothesis.

Objective: This trial was designed to evaluate the efficacy and safety of diluted nitrous oxide in the treatment of acute pain caused by rehabilitation training in burn patients.

## Method

### Design

This study was a single-center, randomized, controlled, double-blind trial that has been registered with the Chinese Clinical Trial Registry (CTR2400089173). The trial protocol was drafted following the checklist of CONSORT statements and SPIRIT Trials guidelines. In this trial, a superiority test will be used and patients will be randomly assigned to two protocol groups at a ratio of 1: 1; Recruitment will begin in April 2025. The schedule of enrolment, and interventions are shown in Fig 1, and the data collection phases of the CONSORT flow chart is shown in Fig 2.

**Fig 1 pone.0333378.g001:**
[figure not shown]
Schedule of inclusion, interventions and assessments. The leftmost column indicates the contents of recruitment, intervention and evaluation, the checkbox indicates the operation at the corresponding time point, and the rightmost column indicates the evaluation method.

**Fig 2 pone.0333378.g002:**
[figure not shown]
The CONSORT flow chart. Patient absence and reasons during recruitment, randomization assignment, assessment and analysis are described.

### Ethics and communication

This trial will strictly comply with the Declaration of Helsinki to ensure the rights and safety of participants

This study has been approved by the ethics committee (2024−054)All participants will sign the informed consent form in writing after fully understanding the purpose, methods, risks and benefits of the study.All information and data collected during the study will be kept strictly confidential and used exclusively for this study. Data will be anonymized to protect patient privacy.Patients have the right to withdraw from this study unconditionally at any time.The results of the study will be disseminated to the public through relevant academic journals and conferences.

### Participants

All patients with pain caused by rehabilitation training after burn surgery will be invited to participate in this study. In order to reduce complications that may interfere with pain scores during rehabilitation training, we will recruit patients whose burn sites and depths are relatively consistent or close, and the therapists should have more than two years of working experience in the burn department. The inclusion criteria are as follows: men or women at least 18 years old who are willing to participate in the trial and sign the informed consent form; Start functional exercise 3–6 weeks after surgery (with or without skin grafting); Worst pain reported during rehabilitation exercise ≥ 4 (0–10 cm on the visual analog scale (VAS)); There were no postoperative complications. Exclusion criteria included the following: non-primary burn patients; Patients with unconsciousness or abnormal mental status that makes it difficult to report pain scores; Patients with residual wounds or active infections in the scar area; Patients with severe inflammation of the treated area; Patients with contraindications to N_2_O (epilepsy, pneumothorax, lung cancer, chronic obstructive pulmonary disease and acute respiratory infections, abdominal distension or suspected intestinal obstruction, severe inhalation injury, drug-induced or pathological pulmonary fibrosis, maxillofacial injury, diseases involving the ear, nose, throat, e.g., sinuses, otitis media); Drug dependence or abuse; Pregnant or breastfeeding patients.The main inclusion and exclusion criteria are shown in Table 1.

**Table 1 pone.0333378.t001:** Main inclusion and exclusion criteria.

Inclusion criteria	Exclusion criteria
Burn patients with acute pain caused by functional exercise starting 3–6 weeks after surgery	Patients with psychiatric disorders or altered mental status have difficulty reporting pain
Age ≥ 18 years	Patients with non-first burns
Worst pain reported during rehabilitation exercise ≥ 4 (0–10 cm on the visual analog scale (VAS))	Drug dependence or abuse Pregnant or breastfeeding patients
There were no postoperative complications	Patients with contraindications to N_2_O(epilepsy, pneumothorax, lung cancer, chronic obstructive pulmonary disease and acute respiratory infections, abdominal distension or suspected intestinal obstruction, severe inhalation injury, drug-induced or pathological pulmonary fibrosis, maxillofacial injury, diseases involving the ear, nose, throat, e.g., sinuses, otitis media)

This table lists the inclusion criteria and exclusion criteria. The left side is the inclusion criteria and the right side is the exclusion criteria.

### Recruitment strategies

The programme will be in the burn department of the 960th Hospital of PLA in China Implement, which is a general hospital in Shandong. Patients who undergo rehabilitation exercises after burn surgery will be the source of recruitment. A member of the study team will be in contact with the case manager, patients and relevant staff in the burn unit for information related to the study. Researchers introduce the details of the study to patients and their attending physicians, including the study purpose, methods, risks, and benefits. Patients will contact the researcher if they are willing to participate in this study. Upon assessment, patients who meet the inclusion criteria will sign informed consent. Diluted nitrous oxide and oxygen will be provided free of charge to patients participating in the study. Medical professionals will provide health and safety protection for subjects. If the study has caused loss or inconvenience to the patient, appropriate compensation is given.

### Randomization, allocation, concealment and blinding

Randomization will perform by statistical experts, using SPSS 27.0 software randomly assigned patients 1: 1 to the intervention group versus the control group. The experimental group will be given nitrous oxide inhalation and conventional treatment, while the control group will be given placebo (100% oxygen) inhalation and conventional treatment. Before the trial begins, the project manager will prepare a series of opaque envelopes, each containing a card with treatment assignment written on it (“nitrous oxide group” or “placebo group”). When the patient meet the inclusion criteria and completed the baseline assessment, the project manager will randomly select an envelope from it and determine the allocation of the patient based on the card inside the envelope. Grouping will be confidential to patients and other investigators. The process of extracting the envelope is free from external interference, and the envelope is immediately destroyed to ensure the concealment of the distribution. The devices for both groups of gases are identical in appearance and are both labeled A or B. Neither the investigators nor the subjects involved in the trial could distinguish gases by smell and appearance. A researcher who is not involved in the evaluation will connect the patient to the gas device during the treatment and ensure the proper inhalation of the gas. Assessments will be performed independently by another investigator according to pre-set criteria and time points. During this trial, if the patient has serious side effects and other emergencies, the preset emergency unblinding procedure should be followed, and corresponding treatment measures should be taken to ensure the safety of the patient. Statistical analysts are also unaware of patients’ grouping and treatment measures.

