### Data management and analysis

In order to ensure the accurate entry of data, two independent personnel enter the data respectively and compare them to ensure consistency. In order to improve quality, researchers are trained before studying. The senior academic statisticians in the group regularly checked the data, including missing values, outliers, etc., and corrected them in time.Missing data from subjects who withdraw from the study will be imputed using multiple imputation methods. Shortly after project initiation, a data monitoring committee (DMC) composition and audit system will be established to monitor data collection and management and patient safety throughout the study. Four professional therapists and nurses, two pain management specialists, and a senior academic statistician who serves as chair of the board will serve as members. Patient safety is monitored and managed by professional therapists and pain management experts.All information will be stored confidentially in the office. Replace all identifying information of the participant, such as name and gender, with a code and always keep it confidential, with only the project manager or attending physician knowing the patient’s personal information. In addition, none of the reports about this study will disclose the personal information of patients.

Statistical analysis will perform using spss.27, with an alpha set at 0.05. The mean (standard deviation), median (interquartile range), minimum value, maximum value and proportion (95% confidence interval) of quantitative data will be listed, and the count data will be described in quantity and percentage. Mean comparison between the two groups will be performed using t-test (normal distribution) and Mann-Whitney test (non-normal distribution). Chi-square test will be used to compare proportions.A value of P < 0.05 will be considered statistically significant.

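### The arm is set by a hand-picked envelope that is then destroyed, so assignments cannot be checked against the SPSS sequence, and the abstract describes different envelope handling

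*Protocol article*

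**What the plan says.** The section on randomization, allocation, concealment and blinding opens with the generation step: "Randomization will perform by statistical experts, using SPSS 27.0 software randomly assigned patients 1: 1 to the intervention group versus the control group". It then turns to envelopes: "the project manager will prepare a series of opaque envelopes, each containing a card with treatment assignment written on it". The cards name the arm in plain words. Once a patient is eligible and baseline is complete, "the project manager will randomly select an envelope from it and determine the allocation of the patient based on the card inside the envelope". Afterwards, "the envelope is immediately destroyed to ensure the concealment of the distribution". The same section says that the gas devices are labelled A or B, and it refers to a preset procedure for emergency unblinding.

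The Method paragraph of the abstract states: "Doctors, therapists, patients, and data collectors were unaware of the assignment outcomes". It also says: "The nurse performing the intervention handed the envelope with the patient code and the A or B assignment to the physician". Earlier in that paragraph the letters are defined: A is the nitrous oxide group and B the oxygen group.

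The data management section adds that identifying information is coded, "with only the project manager or attending physician knowing the patient’s personal information".

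**The concern.** Two steps are each described as assigning the patient: a computer-generated 1:1 assignment and a random pick from a set of envelopes. Only one of them can fix the arm, and the text gives that role to the pick. The person who picks also filled the envelopes and is one of two roles with access to patient identity. The stated purpose of destroying the envelope is concealment, but destruction comes after the assignment is known.

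The trial is single-centre, and its primary outcome is a self-reported VAS score, which the Limitation section itself calls subjective. Sound allocation is then the main protection against systematic differences between the arms, and analysis cannot restore it afterwards. At stake is whether the sponsor could show a reader or auditor that each patient received the arm that a fixed sequence had set for them.

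**Working it through.** No figure in the document depends on the allocation mechanism, so the check is a comparison of the text.

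**1. SPSS list against hand pick.** A list controls allocation only if its entries are used in order. The protocol says that the envelope is picked at random and that its card decides. SPSS can then fix at most how many cards of each kind exist, or what is written on them. It cannot fix which patient gets which card. With no order, there is nothing to compare a realised assignment with.

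**2. Destruction against its stated purpose.** Concealment means that nobody involved can know the next assignment before the patient is entered. The opaque envelope serves that purpose. Once it is opened the assignment is known, so destroying it adds no concealment. It does remove the object that could show which envelope was opened for which patient, and whether more than one was opened.

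**3. Abstract against the randomization section.**

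| | Randomization section | Abstract, Method |
|---|---|---|
| Who handles the envelope | Project manager | Nurse who gives the intervention, then physician |
| What it carries | Card naming the arm in words | Patient code and A or B |
| What happens to it | Destroyed at once | Handed on |
| Who is unaware | Patients and other investigators | Includes doctors |

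The same envelope cannot be both destroyed at once and handed on. Because the abstract ties A to nitrous oxide and B to oxygen, a physician who reads the letter and knows that key learns the arm, although doctors are said to be unaware of it.

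**4. What a re-draw would do (illustration only).** The make-up of the envelope set is not stated. Assume equal numbers, k cards per arm, with a drawn card set aside and a second one drawn. The chance that the arm changes is k/(2k − 1):

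- k = 40 (one card per planned patient, at the start): 40/79 = 0.51
- k = 10: 10/19 = 0.53
- k = 2: 2/3 = 0.67

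If the card is put back first, the chance is k/2k = 0.50. On any of these assumptions, a single re-draw changes the arm at least half the time, and no safeguard described in the article would reveal it.

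**5. Patients affected.** The Trial status section gives a recruitment start of 7 April 2025, about 10 patients a month and eight months: 10 × 8 = 80, the planned total. Each month without a change would add about 10 patients under this procedure. The number already randomised cannot be read from the document.

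**The case against.** The strongest reply is that the procedure is still random. Cards could be written from the SPSS output, and an honest draw without replacement is a legitimate form of random allocation. That stands. The defect is that the result cannot be checked against a fixed order, not that allocation is non-random.

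Second, a reader might infer that no record of assignments survives. The document does not support this. Only the envelope is said to be destroyed. Emergency unblinding needs a retained link from patient to arm, and four weeks of daily gas cannot be delivered without one. But such a link shows the final arm, not whether it came from the first envelope opened. The audit system in the data management section is described for data collection, data management and patient safety, not for allocation.

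Third, a reader might infer that the envelopes carry no numbers. The article is silent, and a condensed article may leave that out. The point rests on the stated random pick, which would make any numbering idle.

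Fourth, a reader might infer that the project manager could predict the next card and steer enrolment. That needs a known card pool and control over who enters. The pool is not stated, and the recruitment section gives recruitment to researchers and a study team member without naming the project manager. The draw also follows eligibility and baseline. No claim about predictability is made here.

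Finally, the abstract's sentence may describe later communication of a masked code rather than a separate way of allocating. That is possible. Even so, it leaves the physician's blinding and the fate of the envelope unclear, so the two sections still have to be reconciled.

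**Conclusion.** The point holds as a weakness in a procedure that the article states, not as a detail left to a fuller document. The hand pick means that the SPSS order does not decide who gets which arm. Destroying the envelope does not serve the purpose given for it and removes physical evidence. The abstract and the randomization section describe different handling.

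The weakness reaches every patient allocated this way, up to the planned 80. No amount of bias can be estimated, because nothing suggests that re-drawing or swapping has taken place or is intended. The re-draw chances above depend on an assumed card pool and show only what an undetected re-draw could do. The conclusion assumes that the article describes the procedure actually in use. If the envelopes are in fact opened in list order and kept, the text needs correcting rather than the conduct.

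**What to change.** For patients not yet randomised:

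- Let the SPSS list fix the contents of sequentially numbered, sealed opaque envelopes.
- Have them prepared by someone already on the team who does not enrol, treat or assess patients, for example the statistician who generates the list. That person should not be the blinded analyst, since analysts are said to be unaware of grouping.
- Open the next number only after baseline is complete and the patient code has been written on the envelope.
- Keep the opened envelopes and cards with an allocation log, out of reach of blinded staff.

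Rewrite the abstract and the randomization section so that they give one account of who handles the envelope, what it carries, what happens to it and who is blinded. For patients already randomised, document how each assignment was made and what record exists. The change cannot repair those assignments, but it makes the report honest about them.

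The cost is a short amendment and modest record keeping during recruitment. The list for the remaining patients must also take account of the assignments already made if 40 per group is still the aim. No particular type of randomisation list is required for this point.
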